#### Usual care group

Participants who are randomly assigned to the control group will receive standard care from their existing nephrologists, nurses, and clinical staff. As all of the participants in the study will be receiving ESA therapy, this care may include a description of the purpose of the medication by the staff member administering the injection and counseling about its purpose and potential risks, but without use of the ESA decision aid.

#### Intervention group

Participants randomly assigned to the intervention group will receive a paper copy of the ESA decision aid (Fig. 3). This decision aid will be administered by and discussed with a nephrology nurse practitioner, who will explain the purpose and function of ESA’s, the goal hemoglobin levels for those receiving ESAs, the positive and negative effects of the medication, and additional resources available to patients. In order to maintain consistency across the clinics, the same nurse practitioner will administer the decision aid tool to all intervention participants across the dialysis clinics. Similarly, a nurse in the CKD clinic that is assigned to anemia management will be responsible for administering the ESA decision aid. Each of these clinical personnel will be trained and oriented to the content and recommended use of the decision aid.

### Data collection, follow-Up, and outcomes

#### Measures assessed

All participants will be assessed using in-person questionnaires at baseline before or after their study visit and at 3 months after enrollment, as described in Table 1. Changes in patient scores that occur between baseline pre-visit and after the administration of the ESA decision aid will be compiled and analyzed. Additionally, all patients’ medical records will be abstracted for relevant comorbidities, lab values, medications, and vital signs at both baseline and 3 month study visits. In this minimal risk study monitoring for any reported associated adverse events such as anxiety with the educational intervention will be performed throughout its duration by the PI and study team. All available efforts will be made to blind outcome survey assessors from group assignment.

#### Data management, privacy and monitoring

Data will be entered into a secure online database by the study coordinator. To protect patient confidentiality, study-specific identification numbers will be used in the study database in lieu of participant identifying information. Only the PI and the study coordinator will have access to the study identification/patient identification link log, which will be destroyed after study completion. The PI will monitor data quality and data queries will be resolved by the study coordinator. Due to the low risk profile of the study, ARC-KD will not convene a data monitoring committee.

### Statistical considerations

#### Data analysis

The randomly assigned intervention or control group will be the primary independent variable for intention to treat analysis. Multiple imputations will be used to handle missing data. Evaluation of the primary outcome of patient anemia knowledge will be determined by comparing intervention and control group Patient Anemia Knowledge in Kidney Disease (PAKKD) [19] survey scores between baseline pre-visit and post-visit as well as baseline pre-visit and 3 months post-intervention for both study arms. Evaluation of the secondary analyses of provider communication satisfaction, health decisional certainty and perceived self-efficacy in patient-provider communications and patient kidney care will be similarly measured and analyzed using the Communication Assessment Tool (CAT) [20], Decisional Conflict Scale (DCS) [21] and Perceived Efficacy in Patient-Physician Interactions (PEPPI) [22] surveys, respectively. Baseline pre-visit variables will be compared between the study arms to assess the successfulness of randomization including gender, age, education and race, using median and interquartile ranges for continuous variables and frequencies and proportion for categorical variables to ensure homogeneity. Chi-squared tests for categorical variables and Wilcoxon-rank sum test for continuous variables will be used to assess the differences in baseline data between intervention and control. We will use linear regression models to compare the change in the PAKKD anemia knowledge scores from baseline to post-visit and baseline to 3 months post intervention between the study arms. Baseline pre-visit values of the outcome variable will be included as a model covariate in linear regression analysis to compare changes from baseline pre-visit. Lastly, planned exploratory analyses include performing logistic regression analysis to assess association between the likelihood of achieving or maintaining hemoglobin targets.

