### Phase 2: randomized controlled trial evaluating the use of an ESA decision aid to improve patient anemia knowledge

To evaluate the ESA decision aid in practice, we will conduct a randomized controlled trial of 100 patients. The trial will utilize validated survey tools and measures to determine if the primary and secondary outcomes of increased patient knowledge and patient satisfaction with ESA use decision have been met, respectively (Table 1).

**Table 1 Tab1:** Study outcomes, measures, and patient characteristics

No.	Outcomes, Measures & Characteristics	Data Source by Outcome	Timeline and Frequency		
			Baseline Pre-Visit	Post-Visit	Three Months
1	Primary Outcome	*Patient Knowledge*			
	Anemia Knowledge	Patient Anemia Knowledge in Kidney Disease (PAKKD) [19]	X	X	X
2	Secondary Outcomes	*Patient Satisfaction*			
	Provider Communication Satisfaction	Satisfaction with Provider Communications (CAT) [20]		X	
	Health Decision Certainty	Decisional Conflict Scale (DCS) [21]		X	
	Perceived Communication Efficacy	Perceived Efficacy in Patient-Physician Interactions (PEPPI) [22]		X	X
3	Subject Characteristics	*Potential* *Co-Variables*/*Modifiers*			
	Patient Demographic Information	Demographic Form	X		X
	Patient Numeracy Assessments	Schwartz Risk Numeracy Test [27]	X		
	Anemia Symptoms	Functional Assessment of Chronic Illness Therapy-Fatigue (FACIT-F) [28]	X		X
	Medical Outcomes	Patient Electronic Medical Record Hemoglobin Lab Values	X		X

Following informed consent, ARC-KD study participants will complete the indicated survey metrics during at least one of three possible time points: enrollment (Baseline Pre-Visit), up to one week after the baseline enrollment visit (Post-Visit) and three months after enrollment (Three Months). Study staff will obtain hemoglobin lab values from each participant’s electronic health care record at baseline and three months.

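### Baseline significance tests cannot show whether randomization succeeded; they should be dropped, and a short fixed covariate set would be a near-free gain

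*Protocol article*

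**What the plan says.** All of this is in the protocol article. The Data analysis section states: "Baseline pre-visit variables will be compared between the study arms to assess the successfulness of randomization including gender, age, education and race". That sentence goes on to give the summaries, "using median and interquartile ranges for continuous variables and frequencies and proportion for categorical variables to ensure homogeneity". The next sentence adds the tests, which compare the two arms: "Chi-squared tests for categorical variables and Wilcoxon-rank sum test for continuous variables will be used to assess the differences in baseline data".

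For the primary outcome the section says: "We will use linear regression models to compare the change in the PAKKD anemia knowledge scores from baseline to post-visit", and likewise to 3 months. On adjustment it says: "Baseline pre-visit values of the outcome variable will be included as a model covariate in linear regression analysis". No other covariate is named.

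Table 1 lists demographics, a numeracy test, FACIT-F and hemoglobin under a block for possible covariates or modifiers, all measured at baseline. The Randomization section describes a computer-generated sequence with secure allocation, to which the recruiting coordinator is blind. It has no blocking by site, and no stratification is described.

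**The concern.** When allocation follows a concealed, computer-generated sequence, any baseline difference between arms arises by chance. A p-value for that difference then tests a hypothesis that the design already makes true. It cannot grade the randomization, and it does not measure whether an imbalance matters for the outcome, which depends on the size of the imbalance and on how strongly the variable predicts PAKKD.

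The tests can mislead in two ways. A small p-value may be reported as a failed randomization when nothing went wrong. A set of large p-values may be reported as proof that the arms are alike, when in a trial of 100 a difference of some size can pass unnoticed.

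The better protection against chance imbalance is adjustment fixed in advance. The stated model already has the most obvious covariate, baseline PAKKD. Education and numeracy are also measured at baseline and are plausible predictors of a knowledge score, but the only use the section states for education is the balance comparison.

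**Working it through.** **Inputs.** From the article: 100 participants (Phase 2; Sample size and power); PAKKD SD of 20 points, minimum detectable difference of 11 points, 80% power, two-sided (Sample size and power); four named baseline variables (Data analysis). Assumed: 50 per arm, since no allocation ratio is stated; level 0.05, since no value is printed; independent baseline tests; all correlations and R² values.

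**Step 1. The plan's own figure.** MDD = (1.96 + 0.842) × 20 × √(2/50) = 11.2 points, which rounds to the stated 11. Power at exactly 11 points is 0.785 (normal approximation) or 0.777 (t-test). The stated figure is reproduced, which supports 50 per arm and 0.05 as working assumptions.

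**Step 2. False alarms under sound randomization.** P(at least one p<0.05) = 1 − 0.95^k.
- k = 4 (the named variables): 1 − 0.95⁴ = 0.185.
- k = 8 (illustrative, because the article's list is open-ended): 1 − 0.95⁸ = 0.337.

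Correlated variables would change these figures somewhat.

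**Step 3. False reassurance.** The largest standardized difference that stays non-significant is about 1.96 × √(2/50) = 0.39 SD (normal approximation). For a binary factor at 50% prevalence it is 1.96 × √(0.5 × 0.5 × 2/50) = 0.196, or about 20 percentage points.

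If such a factor correlates r with PAKKD, the shift in an unadjusted difference is r × 20 × 0.392:

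| r (assumed) | shift, points |
|---|---|
| 0.2 | 1.6 |
| 0.3 | 2.4 |
| 0.4 | 3.1 |

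The target difference is 11 points. These shifts are upper illustrations: the planned model adjusts for baseline PAKKD, which would remove part of them.

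**Step 4. What further covariates could add.** If they explain a share R² of the variance left after baseline PAKKD, the standard error is multiplied by √(1 − R²), and the equivalent sample size by 1/(1 − R²).

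| R² (assumed) | SE factor | SE reduction | equivalent N factor |
|---|---|---|---|
| 0% | 1.000 | none | 1.00 |
| 10% | 0.949 | about 5% | 1.11 |
| 20% | 0.894 | about 11% | 1.25 |

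In power terms, let ρ be the correlation between baseline and follow-up PAKKD (also assumed), so that the residual SD is 20 × √(1 − ρ²) × √(1 − R²). Power for 11 points with 50 per arm is then:

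| ρ | R² = 0% | R² = 10% | R² = 20% |
|---|---|---|---|
| 0.3 | 0.822 | 0.860 | 0.897 |
| 0.5 | 0.888 | 0.917 | 0.944 |
| 0.7 | 0.971 | 0.982 | 0.990 |

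Most of the available gain comes from baseline PAKKD when ρ is moderate or high, and that covariate is already planned.

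**The case against.** Four points can fairly be made for the plan.

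1. The purpose of checking randomization, and the phrase about homogeneity, stand in the sentence on descriptive summaries. The sentence on tests speaks only of assessing differences. This is correct as grammar, but the two sentences are consecutive and describe one comparison, and no other purpose is given for the tests. The point stands.

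2. Calling the null true presumes that allocation was carried out as designed, which is what such a check might question. That is fair, but a handful of tests at 50 per arm is a weak detector of faulty allocation. Comparing assignments with the generated sequence would answer the question directly.

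3. Nothing is said to follow from a baseline p-value. A reader might infer that the tests will select covariates; the article does not say so, and the one named covariate is fixed beforehand. This objection stands in full and limits the size of the concern.

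4. Covariates beyond the baseline outcome are commonly settled in a statistical analysis plan, which is not shown, so their absence from an article is not an error. This also stands. The covariate suggestion is an improvement, not a correction.

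Two stronger readings should be resisted. A reader might infer that the primary model ignores baseline prognosis; it does not, because baseline PAKKD is in it. A reader might also infer from the 3-month marks in Table 1 that later FACIT-F or hemoglobin values will be adjusted for. Those marks are a collection schedule, and no such adjustment is planned.

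**Conclusion.** The concern holds for the baseline tests. They do not serve the purpose given for the comparison: about 18.5% of sound randomizations would show at least one significant difference over the four named variables, and imbalances up to about 0.39 SD would go unflagged. These figures rest on independent tests, a 0.05 level and 50 per arm.

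The consequence is for interpretation and reporting. The tests do not bias the treatment estimate, and leaving out further covariates costs some precision, not validity. The gain from adding them cannot be fixed from the documents, which give no prognostic strength for numeracy, education or setting. It runs from nothing to a standard error about 11% lower over the assumed 0% to 20% range.

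**What to change.** 1. Delete the chi-squared and Wilcoxon baseline tests, together with the wording that the comparison assesses the success of randomization or ensures homogeneity. Keep the table of medians, interquartile ranges, frequencies and proportions by arm.

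2. As an improvement, keep baseline PAKKD in the linear model and add baseline numeracy score and education as fixed covariates, optionally with dialysis versus CKD clinic. State that they are included whatever the observed balance, and use the same set for the post-visit and the 3-month comparison.

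Cost: a change of wording. Numeracy and demographics are already scheduled at baseline in Table 1. Clinic type is not listed there but is known from the recruitment sites. Beyond baseline PAKKD the model uses one degree of freedom for numeracy, at least one for education (its levels are not stated) and one for a two-level setting, so a few out of 100. If the added variables explain nothing, that is the only loss.

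Nothing needs to be changed about 3-month FACIT-F or hemoglobin on this point.

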**Methods:**

Using the principles of informed shared decision making theory, we designed and piloted an ESA decision aid intended to increase CKD and ESRD patient understanding of the potential risks and benefits of ESAs. Informed by the findings during development, the ESA decision aid was modified and finalized for testing. We will perform a randomized clinical trial to assess if administration of the ESA decision aid improves patient understanding of the risks and benefits of ESA use compared to control patients receiving standard care. Participants with either CKD or ESRD and who are receiving ESAs will be eligible for participation. The primary outcome is patients’ score on the Patient Anemia Knowledge in Kidney Disease (PAKKD) survey assessed at enrollment and 3 months after. Secondary outcomes include decisional conflict related to ESAs, and patient satisfaction with provider communication.

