#### Sample size and power

We are aware of no other previous studies examining the effectiveness of a shared decision-making intervention designed for the use of ESAs in CKD or ESRD. Based upon previous experience of using a brief educational worksheet to improve general kidney knowledge [23], we estimate a possible doubling or tripling improvement in the odds of improved kidney health knowledge. For the primary outcome of the PAKKD anemia knowledge score (range: 0–100 %), preliminary data have showed a mean (standard deviation) improvement of 59 % (20 %) [19]. Using a *t*-test for independent samples, the calculated minimum detectable difference is 11 % (59 % in control, 70 % in intervention), showing 19 % relative improvement in anemia knowledge score with 80 % power at a 2-sided significance level. For the purposes of this study, the proposed sample size of 100 participants should be adequate and informative.

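### The primary time point for the anemia knowledge score is stated inconsistently: 3 months in the Abstract, post-visit and 3 months unranked in the analysis section, and unspecified in the power section

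*Protocol article*

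**What the plan says.** Four places in the protocol article bear on when the primary outcome is judged.

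- **Abstract, Methods.** The primary outcome is the score on the PAKKD "survey assessed at enrollment and 3 months after". No post-visit assessment is mentioned.
- **Phase 2 section, Table 1 and the text below it.** PAKKD is the only measure listed under the primary outcome. It is marked at baseline, post-visit and three months. The two follow-up times are described as "up to one week after the baseline enrollment visit (Post-Visit) and three months after enrollment (Three Months".
- **Data analysis.** The primary outcome is evaluated by comparing the arms' "survey scores between baseline pre-visit and post-visit as well as baseline pre-visit and 3 months post-intervention for both study arms". Linear regression models, with the baseline value as a covariate, then compare the "change in the PAKKD anemia knowledge scores from baseline to post-visit and baseline to 3 months post intervention between the study arms". Neither contrast is put first, and nothing says whether one or both must be positive.
- **Sample size and power.** An independent-samples t-test is used: "the calculated minimum detectable difference is 11 % (59 % in control, 70 % in intervention"), "with 80 % power at a 2-sided significance level". The time point is not given, and neither is the numerical significance level.

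The Measures assessed section adds a looser wording: change from baseline to some point after the aid has been given, with no time attached.

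**The concern.** A reader cannot tell which comparison decides the trial. The Abstract points to one contrast, the analysis section to two of equal standing, and the power calculation to one that is not identified.

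The two times answer different questions. The post-visit score, taken up to a week after a one-to-one session with a nurse or nurse practitioner, reflects what was taken in. The 3-month score reflects what was kept. A short-lived gain is a plausible result for an educational intervention. With that pattern, the analysis section would allow a primary success to be reported on the post-visit change, while the Abstract would call the trial negative. Unless the priority is fixed beforehand, it can be chosen after the results are known. Depending on the rule adopted, either the false-positive rate for the primary claim or the power for it would differ from what the power section implies.

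**Working it through.** **Inputs.** From the article: 100 participants, two arms, SD 20 points, 80% power, two-sided test, detectable difference 11 points (59 against 70). Assumed: equal allocation (50 per arm; the ratio is not stated), alpha 5% (no number is given), and the correlation between the two test statistics (not given, so a range is shown).

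**Step 1: reproduce the plan's figure.** Detectable difference = SD × √(2/n) × (z for alpha + z for power).

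- Alpha 5% two-sided: 20 × √(2/50) × (1.960 + 0.842) = 4 × 2.802 = 11.2. By noncentral t it is 11.3. Both round to the stated 11.
- Alpha 10% two-sided gives 10.0 and alpha 1% gives 13.9 (noncentral t). Of the levels tried, only 5% reproduces 11.
- Relative gain: 11/59 = 18.6%, stated as 19%.

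The stated figure is therefore what one comparison at two-sided 5% supports.

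**Step 2: if success at either time counts.** With both tests at two-sided 5%, family-wise error = 1 − P(|Z1| < 1.96 and |Z2| < 1.96), where Z1 and Z2 are bivariate normal with correlation r. At r = 0 this is 1 − 0.95² = 0.0975.

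| r (assumed) | Family-wise error |
|---|---|
| 0 | 9.75% |
| 0.3 | 9.5% |
| 0.5 | 9.1% |
| 0.7 | 8.4% |
| 0.8 | 7.8% |
| 0.9 | 7.0% |
| 1 | 5.0% |

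The same patients contribute to both tests and both models use the same baseline covariate, so positive correlation is expected and 9.75% is an upper figure.

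**Step 3: if both times must succeed.** The chance of a false primary claim does not exceed 5%. Power falls instead. If each test has 80% power, joint power is 0.80 × 0.80 = 0.64 at r = 0. It rises toward 0.80 as r approaches 1, and reaches 0.80 only there.

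**Step 4: what each repair does to the design.**

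- One primary time point: alpha stays at 5%, so the detectable difference stays at 11.2 to 11.3.
- Both kept, with a Bonferroni split at 2.5% each: 4 × (2.241 + 0.842) = 12.3, or 12.5 by noncentral t. Power for 11 points at 50 per arm drops to 0.69 (normal) or 0.68 (t). Regaining 80% takes 63 per arm (normal) or 65 (t), that is 126 or 130 in total.

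These figures ignore any precision gained from the planned baseline adjustment, as the article's own t-test does.

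**The case against.** Several points on the other side have force.

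- **The success rule is not written.** A reader might infer that the trial has two chances to succeed and hence an error rate near 10%. The article says only that both changes are evaluated. If both must be positive there is no inflation. This stands: the error figures are conditional.
- **Error control may be specified elsewhere.** A reader might infer that the trial has none. This is a condensed article, and an analysis plan that is not shown may hold an ordering or an alpha split. This stands too: the absence of a multiplicity rule here is not itself the point.
- **The Abstract may only be abbreviating.** Its wording reads as an assessment schedule, and Table 1 and Data analysis agree with each other. That makes the conflict milder but does not remove it. The Abstract attaches the schedule to the primary outcome and leaves out a time that the body treats as equally primary. Even with the Abstract set aside, the body ranks neither contrast, while the power section sizes one.
- **A fading gain is not a false positive.** If the aid really raises knowledge for a week, a positive post-visit result is true. This is correct. The difficulty there is which claim the trial may make, which is separate from type I error.
- **The sample size is not wrong.** The 11-point figure reproduces and would serve either time point if the SD is similar. A reader should not infer an error in that calculation.
- **Another order would work.** Testing post-visit first and 3 months second controls error equally well. The choice is scientific and belongs to the investigators.

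**Conclusion.** The point holds as an inconsistency in the primary time point, visible in the article itself: one time in the Abstract, two unranked times in Table 1 and Data analysis, and one unidentified comparison in the power section. Omission from a condensed article does not explain it, because these are positive statements that do not agree.

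Its size depends on the missing rule. Under an either-time rule, with each test at two-sided 5%, the family-wise error is about 7.0% to 9.75% for correlations from 0.9 down to 0. Under a both-times rule, error is protected and joint power is below the 80% quoted. The 5% level, equal allocation and the correlations are assumptions, the first supported by its reproducing the 11-point difference. The documents do not show that the trial's error rate is inflated, only that the text leaves this open.

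Severity: should be fixed. The repair is simple before the results are known and hard to make credible afterwards.

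**What to change.** Name one primary time point and use it in the Abstract, Table 1, Data analysis, and Sample size and power. Three months is the natural choice because the Abstract already gives it. Analyse it with the planned baseline-adjusted linear regression at a stated two-sided alpha of 5%, and say that the 11-point detectable difference refers to that comparison.

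Make the other time point a secondary endpoint, for example tested at 5% in fixed sequence only if the primary test is significant. If the investigators regard immediate understanding as the main question, the reverse order is equally valid, provided the Abstract is changed to match.

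The cost is wording: no added patients, visits or data, and the stated detectable difference is unchanged. The downside is that a difference seen only at the non-primary time can no longer be claimed as primary success, and under a fixed sequence it would not be formally tested.
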